##### 2.7.2.7 Physical Activity and Sedentary Behavior

Physical activity and sedentary behavior are additionally assessed using the ActiGraph wGT3X-BT (*ActiGraph LLC, Pensacola, FL*) at all testing time points. Participants wear the accelerometer on their hip for seven consecutive days excluding water-based activities and sleep. ActiLife software (*ActiLife 6; ActiGraph LLC*) is used to analyze the ActiGraph data. Only wake wear time is used with a minimal data collection period set for inclusion in analysis of four days of at least 600 minutes per day. Non-wear time is excluded from the analysis, defined as ≥90 minutes of consecutive zeros with a 2-minute spike tolerance (59). Commonly used cutoff points among cancer patients will be used to classify sedentary time (<100 counts per minute), light physical activity (100–1951 counts per minute), and moderate-to-vigorous physical activity (≥1952 counts per minute) (60–62).

##### 2.7.2.8 Patient-Reported Outcomes

Health-related quality of life (QOL) is assessed using the Functional Assessment of Cancer Therapy-Breast (FACT-B) questionnaire. The FACT-B is comprised of 44 items to specifically assess QOL in breast cancer patients (internal consistency coefficient of α = 0.90) (63). The Brief Fatigue Inventory (BFI) is used to rapidly assess the severity and impact of cancer-related fatigue including six items that correlate with QOL measures (internal consistency coefficient of α = 0.96) (64). Depressive symptoms are assessed using the 20-item Center for Epidemiologic Studies Depression (CES-D) scale, which was designed to measure one’s current level of depressive state (internal consistency coefficient of α = 0.82) (65, 66). The State-Trait Anxiety Inventory (STAI) is a 40-item questionnaire, which will be used to examine anxiety, with a consistency coefficient of α = 0.86-0.95 (67). Sleep quality is assessed using the Pittsburg Sleep Quality Index (PSQI) which contains 19 questions evaluating seven domains of sleep: subjective sleep quality, sleep latency, sleep duration, habitual sleep efficiency, sleep disturbances, use of sleep medication, and daytime dysfunction (internal consistency coefficient of α = 0.83) (68, 69). The Brief Pain Inventory – short form (BPI) is used to assess the impact of pain on QOL. The BPI includes a sensory and reactive dimension and has been previously validated in breast cancer survivors (internal consistency coefficient of α = 0.81-0.89) (70, 71). Barriers to recruitment and exercise adherence are assessed using the 17-item Barriers to Recruitment Participation Questionnaire (BRPQ) (72), and the 43-item Exercise Benefits/Barriers Scale (EBBS) (73). Participant burden is assessed using the 21-item, Perceived Research Burden Assessment (PRBA) (internal consistency coefficient of α = 0.87-0.96) (74).

##### 2.7.2.9 Cognitive Function

Cognitive function is only assessed at baseline, post-phase 1, post-phase 2, and post-phase 3 to prevent familiarization with the cognition-based questions. To assess executive functioning and abilities including response inhibition, cognitive flexibility, working memory, planning, insight, social cognition and behavior, and verbal fluency, we use the NIH toolbox (www.nihtoolbox.org) and the Montreal Cognitive Assessment to assess global cognition. Within the NIH toolbox the following tests are administered: Auditory Verbal Learning Test for immediate recall (memory), Picture Sequence Memory Test for episodic memory, Oral Reading Recognition for language, Flanker for executive function and attention, List Sorting Test for working memory, Oral Symbol Digit Test for processing speed, Dimensional Change Card Sort Test for executive function, and Pattern Comparison for processing speed. We also include an episodic memory composite that is derived from tests examining the hippocampus and surrounding medial temporal lobe (75).

##### 2.7.2.10 Peripheral Neuropathy

Peripheral neuropathy is measured through two tests: 1) Semmes-Weinstein Monofilament Examination (SWME), and 2) vibration testing by the on-off method (76–78). For both tests, participants are seated in an upright position with their eyes closed and socks and shoes off. The SWME is used to evaluate protective sensation at two sites: 1) pad of the great toe (foot), and 2) pad of the index finger (hand), where the nylon monofilament is applied four times to each site and the participant verbally identifies whether the left or right appendage is being touched. The vibration sensation is evaluated by applying a tuning fork to the bony prominences of the great toe, thumb, and medial malleolus where the participant verbally identifies the stopping of the vibration movement. Correct identification of side of the body and on/off vibration sensation for the respective tests is recorded.

#### 2.7.3 Covariates and Other Measures

##### 2.7.3.1 Sociodemographic, Health Behavioral, and Medical Profiles

Sociodemographic, health behavioral, and medical profiles are collected using a set of questions self-reported by the participants.

##### 2.7.3.2 Dietary Intake

Recent dietary patterns are assessed using an automated self-administered 24-hour dietary assessment tool (79). Participants complete three assessments at home on two weekdays and one weekend day, recording all food and drink consumed during the previous 24-hour period. Participants’ consumption of macro- and micronutrients will be analyzed.

##### 2.7.3.3 Activity Logs

The AC group completes a daily activity log for each week throughout the 12-month study period. The ACTIVAS group is asked about their physical activity completed outside of the supervised sessions over the previous week. Additionally, ACTIVAS group completes daily activity logs during the unsupervised and follow-up periods only. The participants are asked to record the type of exercise performed, time spent undertaking the exercise, intensity of that exercise bout (RPE 1-10 Borg scale, or average heart rate for the ACTIVAS group if they are wearing a heart rate monitor), and day of the week it was completed (frequency).

### 2.8 Data Monitoring and Management

Data is monitored internally within DFCI for timeliness of submission, completeness, and adherence to protocol requirements. Monitoring begins at the time of participant registration and continues during protocol performance and completion. The study team collects, manages, and performs quality checks on the data. Potential audits or inspections may be conducted by the principal investigator or their designated representatives. All data is stored on a secure network drive using REDCap, a HIPAA compliant web-based application hosted by Partners HealthCare Research Computing, Enterprise Research Infrastructure & Services, on password protected computers. Any hardcopy data is stored in locked filing cabinets in card access facilities. Results of this study will be presented in publication, conference, and invited speaker formats.

### 2.9 Sample Size Calculation

We propose to randomize 160 subjects (n=80/group). We assume 15% attrition (which is exceptionally conservative given our retention rates of >90%) (80) at the primary endpoint (4-months). With this sample size, we consider the study is sufficiently powered to detect a between-group difference. Specifically, the primary efficacy variable of this study is change in HOMA-IR from baseline to 4-month). From the preliminary results (80), we anticipate the standard deviation of HOMA-IR change from baseline is 6.9. The study will have 80% power, at a two-sided 0.05 alpha level, to detect a 3.3 difference in HOMA-IR change from baseline between the groups.

### 2.10 Statistical Analysis

The primary analysis population is all randomized subjects based on the intention-to-treat principle. The secondary analysis population is the per-protocol set. To test hypotheses related to differences in MetD outcomes across groups at the primary endpoint (4-month), we will use two-sample t-test for the continuous outcomes (HOMA-IR and VA) and Fisher’s exact test for the binary outcomes (diagnosis of metabolic syndrome). For HOMA-IR and VA, we will calculate change from baseline at 4-month for each subject and estimate mean difference between groups and corresponding 95% confidence interval. For diagnosis of metabolic syndrome, we will estimate the proportion of participants with metabolic syndrome at 4-month for each group and compare it between groups. Odds ratios and corresponding 95% confidence interval will be used to summarize the magnitude of the effect of the intervention. ANCOVA and logistic regression models will be also used to compare each of these outcomes at 4-month between groups, conditioning on potential prognostic factors, such as menopausal status, age, BMI, months since end of treatment, history of diabetes, type of treatment (chemotherapy vs radiation vs both), surgery type (lumpectomy, mastectomy), previous history of physical activity prior to diagnosis, and family medical history self-reported.

These primary endpoints are measured longitudinally. We will fit the longitudinal data with generalized mixed-effects models. The identical link and logistic link will be used for continuous and binary outcomes, respectively. The group indicator, time, and other covariates will be included in the models as the fixed effects. Some of the covariates (e.g., menopausal status) will be time-dependent covariates. Measures of physical fitness, functional capacity, and patient-reported QOL outcomes will be also analyzed in the same way.

Subgroup analyses will be conducted to assess the heterogeneity of the intervention effect on each outcome. The following factors will be considered: menopausal status, age, BMI, months since end of treatment, previous diabetes.

The primary analysis would include all completed outcome assessments (regardless of whether the woman stayed on the intervention), inviting those who drop from the intervention to return for outcome assessments. The only missing data here would be those who drop the intervention and do not return for outcome assessments; this includes participants withdrawn due to noncompliance. Preliminary analyses will compare women who do and do not contribute to this analysis on baseline characteristics. A sensitivity analysis will include multiple imputation of all missing outcome data for all time points. While the analytic methods specified for the longitudinal data are likelihood-based and provide valid results when missing mechanism is missing at random, it is possible that missing data may be informative and impact inference of the intervention effect on outcomes. Various sensitivity analyses for missing observations will be performed to assess the robustness of conclusions derived from the primary analysis.

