### 2.5 Randomization and Blinding

After completing all baseline assessments, participants are randomly assigned to either the ACTIVAS exercise group or AC group using a 1:1 ratio and permuted blocked design with varying block sizes to ensure equal numbers of participants allocated to each group where investigators are blinded to this process. Our study biostatistician and co-investigator ([name]) generated the randomization sheet as a cvs file prior to study start-up, after which the research coordinator [name] uploaded the cvs file to a web-based application (REDcap). After baseline testing, one of our research assistants accesses REDCap to conduct randomization. Subsequently, our research assistant informs [name] of randomization result and verbally informs the participant of their group allocation. Randomization is stratified by menopausal status (premenopausal and postmenopausal), which is evaluated at time of diagnosis. Testers and participants are blinded to group allocation during baseline testing, however, due to the nature of the study, it is not possible to blind the investigators or participants to group allocation after baseline. However, testers follow a detailed protocol and are trained in the importance of standardizing outcome assessments and avoiding bias.

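### The 4-month tests (t-test on change, Fisher's exact test) do not condition on baseline or the randomisation stratum; they are valid but give up precision that a baseline-adjusted primary model would probably recover

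*Protocol article*

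**What the plan says.** All references are to the protocol article.

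- **Primary test, continuous outcomes (2.10):** "we will use two-sample t-test for the continuous outcomes (HOMA-IR and VA"). The scale is the change score: "For HOMA-IR and VA, we will calculate change from baseline at 4-month for each subject and estimate mean difference between groups".
- **Primary test, binary outcome (2.10):** "Fisher’s exact test for the binary outcomes (diagnosis of metabolic syndrome"), applied to status at 4 months.
- **Adjusted models (2.10):** "ANCOVA and logistic regression models will be also used to compare each of these outcomes at 4-month between groups". These come on top of the tests above. Their covariates are introduced by "conditioning on potential prognostic factors, such as menopausal status, age, BMI, months since end of treatment, history of diabetes", and several further factors are named after that. The list is given as examples. It includes menopausal status but not baseline HOMA-IR, baseline visceral adiposity or baseline metabolic syndrome status.
- **Randomisation (2.5):** allocation is made "using a 1:1 ratio and permuted blocked design with varying block sizes". On strata the section states: "Randomization is stratified by menopausal status (premenopausal and postmenopausal), which is evaluated at time of diagnosis".
- **Sample size (2.9):** 80 per group, 15% attrition, and "we anticipate the standard deviation of HOMA-IR change from baseline is 6.9". The plan claims 80% power, two-sided alpha 0.05, for a difference of 3.3.

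**The concern.** A change score removes baseline with a slope of exactly 1. ANCOVA estimates that slope from the data. Apart from one degree of freedom, its residual variance therefore cannot exceed that of the change score, and it is smaller unless the true slope is 1. ANCOVA also removes the effect of a chance baseline difference between arms, which a change score over- or under-corrects whenever the slope is not 1.

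The additional ANCOVA does not settle this. It is not the primary test, and nothing commits it to baseline HOMA-IR or visceral adiposity. The stratum is likewise absent from both primary tests. Menopausal status appears only in the additional models, and section 2.10 treats it as time-dependent in the longitudinal ones, which is not the status at diagnosis used for randomisation.

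For metabolic syndrome, eligibility (2.2) does not require the syndrome at entry. The 4-month prevalence therefore mixes women who could remit with women who could only develop it. Baseline status is collected (2.7) but the test does not use it.

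At stake is precision in a trial sized to its power target with no reserve, and clarity about which result governs if the t-test and the additional ANCOVA disagree.

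**Working it through.** **Inputs (2.9).** 80 per group; 15% attrition, so 80 × 0.85 = 68 evaluable per group; SD of change 6.9; difference 3.3; two-sided alpha 0.05.

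**Step 1: reproduce the plan's figure.**
- Standard error of the difference = 6.9 × √(2/68) = 1.183.
- Normal approximation: 3.3/1.183 − 1.96 = 0.83, so power is 79.6%.
- Noncentral t: power 79.1%, detectable difference at 80% power 3.34.
- The stated 80% for 3.3 reproduces.

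**Step 2: ANCOVA with equal SDs at both times.** Let r be the correlation of baseline and 4-month HOMA-IR, and σ² the common variance.
- Variance of change = 2σ²(1 − r).
- ANCOVA residual variance = σ²(1 − r²).
- Ratio = (1 + r)/2, so the effective SD is 6.9 × √((1 + r)/2).

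The documents do not give r, so a range is assumed (noncentral t, 68 per arm, difference 3.3):

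| r | Variance ratio | Effective SD | Power | Detectable difference at 80% |
|---|---|---|---|---|
| t-test on change | 1.00 | 6.90 | 79.1% | 3.34 |
| 0.3 | 0.65 | 5.56 | 93.0% | 2.69 |
| 0.5 | 0.75 | 5.98 | 89.2% | 2.89 |
| 0.7 | 0.85 | 6.36 | 85.2% | 3.08 |
| 0.8 | 0.90 | 6.55 | 83.1% | 3.17 |
| 0.9 | 0.95 | 6.73 | 81.1% | 3.25 |

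A simulation with 68 per arm and 6,000 replicates, fitting baseline and stratum, gave 79% for the t-test throughout and 89%, 85% and 80% for ANCOVA at r = 0.5, 0.7 and 0.9.

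**Step 3: relax the equal-SD assumption.** If the 4-month SD is k times the baseline SD, the ratio is k²(1 − r²)/(1 + k² − 2rk).
- k = 1.2, r = 0.8: 1.44 × 0.36/(2.44 − 1.92) = 0.518/0.520 = 0.997. Power is 79.2%, almost no gain.
- k = 1.2, r = 0.5: ratio 0.871, power 84.3%.
- k = 0.8, r = 0.7: ratio 0.628, power 93.8%.

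**Step 4: the stratum alone.** The documents do not say how prognostic menopausal status is for change in HOMA-IR. If it explained 1%, 5% or 10% of the variance of change (assumed), power by the normal approximation would move from 79.6% to 80.0%, 81.6% or 83.6%.

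**Step 5: metabolic syndrome.** The documents give no prevalence, remission or onset rates. Two assumed sets, both with 60% baseline prevalence and 68 per arm (4,000 simulations), show how far the answer depends on them:
- Persistence 90% v 70%, onset 10% v 7%: Fisher 27%; Mantel-Haenszel by baseline status 59%, or 48% with continuity correction.
- Persistence 80% v 65%, onset 15% v 12%: Fisher 17%; Mantel-Haenszel 30%, or 23% with continuity correction.

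The gap changes severalfold with the assumed rates and the correction, and part of it reflects Fisher's conservatism, not baseline information. No figure should be attached to this outcome.

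**The case against.** The strongest reply is that nothing here is an error. The change-score t-test is an accepted estimator, unbiased under randomisation. It matches the stated primary variable and the SD used for sizing, and the power claim is right. All of that stands.

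A reader might infer that the primary analysis ignores baseline. For HOMA-IR and visceral adiposity the text does not support that: baseline is subtracted for every woman. Only the metabolic syndrome test leaves baseline out, and that is not the outcome on which the trial is sized.

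A reader might also infer that adjustment is absent, or that the baseline outcome has been excluded. Section 2.10 plans ANCOVA, logistic regression and mixed models. Its covariate list is open and includes the stratification factor, and a full analysis plan may name more. What remains is narrower: the article itself fixes unadjusted tests as primary and places the adjusted models second.

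Finally, the size of the gain is not known. Quoting only the low-r end would overstate it, and omitting the stratum may cost almost nothing.

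**Conclusion.** The point holds as a loss of efficiency. The primary 4-month tests do not condition on the baseline outcome or the menopausal stratum, and no baseline-adjusted model is designated primary. With equal variances at both times, conditioning on baseline HOMA-IR would raise power from about 79% to between 81% (r = 0.9) and 93% (r = 0.3). The gain could be near zero with a larger 4-month SD and high r, and bigger than shown with a smaller one. The stratum's own contribution is probably small, and the metabolic syndrome gain cannot be sized from the documents.

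The findings do not support a claim that the t-test is biased, that the sample size is wrong, or that the trial is underpowered by its own assumptions.

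**What to change.** Before analysis, designate as primary an ANCOVA of 4-month HOMA-IR on group, baseline HOMA-IR and menopausal stratum as randomised (status at diagnosis). Use the same model for visceral adiposity. Keep the t-test on change as supportive, and state that the ANCOVA governs if the two differ.

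For metabolic syndrome, use a test stratified by or adjusted for baseline status and stratum (Mantel-Haenszel or logistic regression), with Fisher's test as supportive.

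The cost is a change of wording, with no new data or participants. The sample size can stand, because the t-test calculation is then conservative to whatever extent baseline predicts outcome. There is one real downside: the adjusted odds ratio is conditional and is a different effect measure from the unadjusted one. Report the 4-month proportions and the unadjusted odds ratio beside it.

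### The primary HOMA-IR test is an unadjusted t-test on raw change; adjusting for baseline HOMA-IR and the menopausal stratum would gain power at no cost in data

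*Protocol article*

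**What the plan says.** Section 2.9 (Sample Size Calculation) fixes the endpoint: "the primary efficacy variable of this study is change in HOMA-IR from baseline to 4-month". It plans on these inputs: "We propose to randomize 160 subjects (n=80/group"; "We assume 15% attrition"; "we anticipate the standard deviation of HOMA-IR change from baseline is 6.9". The aim is 80% power at two-sided 0.05 "to detect a 3.3 difference in HOMA-IR change from baseline between the groups".

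Section 2.10 (Statistical Analysis) fixes the test: "we will use two-sample t-test for the continuous outcomes (HOMA-IR and VA". It also fixes the scale: "For HOMA-IR and VA, we will calculate change from baseline at 4-month for each subject", summarized as a difference in means with a 95% confidence interval.

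The same section adds ANCOVA as a further comparison at 4 months. Its covariates are given as an open list of examples that includes menopausal status, age, BMI and history of diabetes. Baseline HOMA-IR is not among them. The longitudinal model keeps the continuous outcomes on their original scale through an identity link.

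Section 2.5 (Randomization and Blinding) allocates "using a 1:1 ratio and permuted blocked design with varying block sizes", stratified by menopausal status as assessed at diagnosis. Randomization follows completion of the baseline assessments.

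**The concern.** A change score uses the baseline value with a fixed coefficient of 1. ANCOVA estimates that coefficient from the data, so it removes more noise whenever the true slope differs from 1. Here baseline HOMA-IR is measured before randomization, yet the primary test uses it only by subtraction. The test also ignores the one factor on which randomization was balanced.

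What is at stake is efficiency on the trial's single powered comparison. A real 3.3-unit effect has about a one-in-five chance of being missed under the planned test, and that chance can be lowered with data already being collected.

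A second question is scale. HOMA-IR is formed from fasting glucose and insulin and cannot be negative, and the planning SD is large. If the measure is strongly right-skewed, a few women with extreme values could weigh heavily on a raw-scale mean difference.

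**Working it through.** **Step 1. Reproduce the plan's figure.** Inputs from section 2.9: 80 per arm, 15% attrition, SD of change 6.9, difference 3.3, two-sided 0.05.

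- Evaluable per arm: 80 × 0.85 = 68.
- Standard error: 6.9 × √(2/68) = 1.183.
- Power: Φ(3.3/1.183 − 1.96) = Φ(0.829) = 79.6% (79.1% with the noncentral t).
- Detectable difference at 80% power: 1.183 × (1.960 + 0.842) = 3.32.

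The stated 80% and 3.3 are reproduced.

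**Step 2. Adjust for baseline.** Let σ be the SD at each visit (assumed equal) and r the baseline-to-follow-up correlation.

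- Variance of change: 2σ²(1 − r).
- ANCOVA residual variance: σ²(1 − r²).
- Ratio: (1 + r)/2, so the residual SD is 6.9 × √((1 + r)/2), which is below 6.9 for every r < 1.

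Worked case, r = 0.5: SD = 6.9 × √0.75 = 5.98; standard error = 5.98 × √(2/68) = 1.025; power = Φ(3.3/1.025 − 1.96) = Φ(1.26) = 90%.

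| Analysis | Variance ratio | SD | Power for 3.3, 68 per arm | n per arm for 80% |
|---|---|---|---|---|
| t-test on change | 1.00 | 6.90 | 79.6% | 69 |
| ANCOVA, r = 0.3 | 0.65 | 5.56 | 93% | 45 |
| ANCOVA, r = 0.5 | 0.75 | 5.98 | 90% | 52 |
| ANCOVA, r = 0.7 | 0.85 | 6.36 | 86% | 59 |
| ANCOVA, r = 0.8 | 0.90 | 6.55 | 84% | 62 |

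The article does not give r, so the range is an assumption. The direction does not depend on equal SDs. With unequal SDs σ₀ (baseline) and σ₁ (follow-up), the variance of change exceeds the ANCOVA residual variance by (σ₀ − rσ₁)², which is never negative.

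**Step 3. What 6.9 says about skewness.** With equal SDs, the per-visit SD is 6.9/√(2(1 − r)): 4.9 at r = 0, 6.9 at r = 0.5, 8.9 at r = 0.7. A non-negative variable can be roughly normal only if its mean is at least about 1.96 SDs, that is about 9.6, 13.5 and 17.5 respectively. The article gives no mean, median or per-visit SD for HOMA-IR, so skewness cannot be settled from it.

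**Step 4. What would follow if HOMA-IR were lognormal (assumption).** Simulation with 68 per arm, SD of change held at 6.9, assumed mean 5 to 20, log-scale correlation 0.5 or 0.7:

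- Type I error of the raw t-test: 4–6% throughout.
- Power for a proportional effect worth 3.3 units: raw t-test 82–88%, raw ANCOVA 91% to nearly 100%, log ANCOVA 94–100%.
- Share of the sum of squares of raw change carried by the five most extreme of 136 women: 57–64% at mean 5, 39–46% at mean 10, 28–32% at mean 20, against 22% for normal data.

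**The case against.** The strongest reply is that nothing here is an error. The t-test holds its type I error, the power statement is right on its own inputs, and ANCOVA is already planned with a covariate list open enough to take in baseline HOMA-IR. All of that stands. But the ANCOVA is not the primary test, and the covariate that brings the gain is not named.

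A reader might go further and infer that an SD of 6.9 shows HOMA-IR to be strongly right-skewed, so that the raw scale wastes most of the power. The article does not support this. The 6.9 belongs to a change score, which can be fairly symmetric. Skewness of the level follows only if the mean is small relative to the SD, and no mean is given.

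Very low power figures for the raw t-test can be produced under lognormal assumptions, but they come from smaller effects. For a 25% reduction (log-scale correlation 0.7), power is 23% at mean 5, where the effect is 0.25 × 5 = 1.25 units, and 91% at mean 15, where it is 3.75 units. At the design's 3.3 units, the planned test meets its 80% even under skew.

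A reader might also conclude that the log scale should be primary. A constant proportional effect on lognormal data is the model that suits log ANCOVA best. When the reduction was confined to the top third of baseline values (average 3.3 units, log-scale correlation 0.7), raw ANCOVA had 90% power against 84% for log ANCOVA at log-SD 0.6, and 93% against 92% at log-SD 0.75. The log scale also replaces a difference in units with a ratio of geometric means, which is not the quantity the sample size was built on.

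**Conclusion.** The concern holds as one of efficiency. The primary analysis is valid and correctly powered as stated, but it is less precise than one the trial can run on the same data. At 68 per arm and a 3.3-unit difference, the gain is roughly 4 to 14 percentage points of power (79.6% to between 84% and 93%) for assumed r from 0.8 down to 0.3. This rests on equal SDs at the two visits. The gain from adding the menopausal stratum is not quantified, because the article gives nothing on how strongly it predicts HOMA-IR.

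The skewness question stays open. HOMA-IR would be clearly right-skewed unless its mean is above roughly 10 to 18 (assumed r = 0 to 0.7). That justifies a planned sensitivity analysis and does not by itself justify a change of primary scale.

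**What to change.** - **Primary analysis:** ANCOVA of 4-month HOMA-IR (or its change) on group, baseline HOMA-IR and menopausal stratum. Report the adjusted mean difference with its 95% confidence interval, so that the 3.3-unit planning figure still applies. Enter the stratum as used for randomization (status at diagnosis), since section 2.10 elsewhere treats menopausal status as changing over time.
- **Supportive analysis:** keep the unadjusted t-test on change.
- **Sensitivity analysis:** pre-specify an ANCOVA of log HOMA-IR on the same terms, reported as a ratio of geometric means.

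The cost is wording in section 2.10 and, if wanted, a line in section 2.9 noting that the sample size was set for the unadjusted test. No visits, samples or participants are added. The change should be recorded before outcomes are compared by group.
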